### Description of the intervention

The intervention consisted in the application of the recommendations of a evidence-based practical clinical guideline developed over 6 months by a team from the research group. The guideline was prepared for the Primary Care Division of the Catalan Institute of Health and which has not yet been distributed.

The basic steps in the intervention are:

1. All individuals accessing the PCC, once the motivating problem of the clinical visit had been resolved, were asked about tobacco consumption, their willingness to quit smoking (the stage of change according to the model defined by Prochaska and DiClemente) and their need for specific help in quitting smoking.

2. Individuals in the pre-contemplation or the contemplation stage were administered a brief motivational interview based on the Rollnick and Butler [8] model and were provided with a leaflet containing motivational information.

3. Individuals in the preparation or action stage who preferred the option of no specific help, received a minimal intervention which included brief advice, a leaflet containing practical information on how to quit, an offer/prescription of nicotine substitute if their nicotine dependence was medium or high, and one follow-up clinical visit or telephone call.

4. Individuals in the preparation or the action stage who requested specific help, received an intensive intervention comprising of 9 scheduled follow-up visits over 1 year wich included behavioral intervention, and use of pharmacological agents (substitutes for nicotine or bupropion according to the characteristics of the subject and their previous experiences as regard quitting smoking). They were provided with a leaflet of practical information on how to quit and another with specif advice on how to use the pharmacological treatment.

5. Individuals in the maintenance stage were provided with reinforcement advice.

All the individuals included in the intervention group had the intervention applied in a period of 6-months after their inclusion in the study. In the case of scheduled visits for smoking cessation and non-attendance, the motive was sought out. The successive interventions were adapted to each person's evolution according to the Prochaska and DiClemente's Stages of Change Model.

All the health care professionals in the intervention group attended a 20 hours course that uses techniques such as role playing, as well as a training session in the practical aspects of the protocol.

Control: The patients in the control group received the usual care in the PCC.

### Outcome measures

Self reported abstinence confirmed by a breath carbon monoxide concentration of 10 parts per millions or less, calculating point prevalence at the end of intervention, then at 1 and 2 years after the beginning of intervention, and continuous abstinence rate for 1 year.

The measurement of breath carbon monoxide was carried out by trained health professionals using Bedfont Scientific Ltd. Smokerlyzers following a pre-established protocol.

Other outcome measures:

• Change of stage in the Prochaska and DiClemente's Stages of Change Model.

• Health-related quality-of-life (HRQoL): Medical Outcomes Study 36-Item Short-Form Health Survey (SF-36) acute version (1-week recall period) in persons who quit smoking at baseline and at 2, 4, 12, 26, 52 and 104 weeks after having quit smoking.

### Data collection

An ad-hoc questionnaire that included data relating to:

• Socio-demographic characteristics (age, gender, educational level, social class according to the classification of the UK Registrar General's social classification (RGSC)).

• Anthropometric data (weight, height, blood pressure).

• Characteristics of individual's tobacco consumption (daily consumption in cigarettes/day, years of smoking, age at the start, time before first cigarette of the day, nicotine dependence measured by the Fagerström test, motivation level measured by the Richmond test), help sought to quit smoking, perceived support or lack from family, friends and co-workers.

• Variables related to the Prochaska – Diclemente transtheoretical model of change: stages, self-change processes, self-efficacy and decisional balance.

• Readiness and willingness to quit (perception of importance, confidence and preparation to quit; Richmond test).

• Morbidity (whether or not related to tobacco consumption) and intensity of use of primary care services.

• Alcohol consumption, use of other recreational drugs and physical exercise.

• Variables related to the smoking intervention provided:

▪ Professional who undertook the intervention (physician or nurse)

▪ Pharmacological treatment used: type, timetable, side effects

• As regards people who managed to give-up smoking:

▪ Ratings of tobacco abstinence symptoms (urges to smoke, irritability/frustration/anger, anxiousness, difficulty concentrating, restlessness, hunger, impatient, craving for cigarette/nicotine, drowsiness, depression/feeling blue, and desire for sweets)

▪ Scale of anxiety and depression (Goldberg test)

▪ MOS-SF-36

This questionnaire was divided in two parts (one clinical and another non clinical) and administered at baseline, at the end of intervention (6 months), and after one and two years from the start. The morbidity and use of services data were obtained by health professionals from clinical records.

In people who gave-up smoking, the specific questions related to the quitting process were assessed again in extra interviews at week 2, and at 1, 2 and 4 months after quitting smoking.

The clinical part of the questionnaire was administered in primary care centers by the health professional involved in the study. The non clinical part was administered by phone by especially trained interviewers who were blinded to the patient group assignment.

### Follow-up period

Two years from the start of the intervention.

Figures 1 and 2 shows: Time-line of the ISTAPS project and ALGORITHM OF THE STUDY.

**Figure 1 F1:**
[figure not shown]
**Time-line of the ISTAPS project**.

**Figure 2 F2:**
[figure not shown]
**Algorithm of the study**.

### Sample size calculation

Based on different assumptions

• Power 80%, alpha 0.05, potential study withdrawal (15%).

• A difference of 5% between the success rate of the intervention (10%) and control group (5%) -> a sample size of 499 in every group was needed.

• A difference of 20% between the success rate of the intervention (30%) and control group (10%) for people in the preparation stage -> a sample size of 110 in the preparation stage in every group was needed. Previous studies in Spain (Grandes et al. 2001) showed that approximately 16% of smokers seen in primary care centres were in the preparation stage, and thus, it was necessary to include 687 smokers in every group to obtain 110 in the preparation stage. As this number is greater than the 499 stated previously, this number is used for input in adjusting for the design effect.

• It was considered feasible that each basic care unit would include some 25 individuals in the study.

• The intracluster correlation coefficients (ICC) for outcome variables in cluster randomization clinical trials on guidelines implementation strategies in primary care are generally below 0,05 [32]. This ICC translates into a cluster size of 25 in a design effect of 2.2.

As such, the definitive sample size for the study would be 3024 patients (1512 in each group) corresponding to 121 basic health-care units (61 in each group, intervention and control).

The sample size calculations were performed with the Granmo program (version 5.2).

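### The 110 preparation-stage smokers per group do not follow from the stated inputs, which give about 70 to 73; the 3024 built on 110 is larger than those inputs require

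*Protocol article*

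**What the plan says.** The Sample size calculation section of the protocol article lists 80% power, alpha 0.05 and 15% withdrawal once, ahead of two comparisons.

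- All smokers, 10% v 5%: "a sample size of 499 in every group was needed".
- Preparation stage: "A difference of 20% between the success rate of the intervention (30%) and control group (10%) for people in the preparation stage", for which "a sample size of 110 in the preparation stage in every group was needed".

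It then takes from an earlier Spanish study that "approximately 16% of smokers seen in primary care centres were in the preparation stage" and scales 110 up to 687 smokers per group. Because 687 exceeds 499, it carries 687 forward and applies a design effect of 2.2 (ICC 0.05, 25 patients per unit). The result is 1512 per group, 3024 in total, in 121 units described as 61 per group. The program is named (Granmo 5.2), but not the formula.

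**The concern.** A difference of 20 percentage points from a 10% base is large, and 110 per group looks high for 80% power. The figure matters because the section uses it to choose which comparison fixes the size of the trial. If 110 is too large, three things follow: the stated reason for 3024 fails, the preparation-stage comparison is wrongly named as the one that sets the size, and the power printed beside the figures is not the power that the planned sample gives. Readers of a null or borderline result, and planners who reuse the figure, would be working from a wrong number.

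**Working it through.** **Inputs.** All come from the Sample size calculation section: power 80%, alpha 0.05, withdrawal 15%, rates 5% v 10% and 10% v 30%, preparation-stage share 16%, ICC 0.05, 25 per unit. Sidedness is not stated. I assume two-sided, so (1.960 + 0.842)² = 7.849.

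**Step 1. Reproduce the plan's 499.** Arcsine formula: n = 2 × 7.849 / h², with h = 2·arcsin√p₂ − 2·arcsin√p₁.
- 5% v 10%: h = 0.1925, n = 423.7 per group.
- With 15% withdrawal: 423.7 / 0.85 = 498.5, rounded up to 499.

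The plan's figure is reproduced exactly, with withdrawal already included.

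**Step 2. Same formula, preparation stage.**
- 10% v 30%: h = 0.5158, n = 59.0 per group.
- With withdrawal: 59.0 / 0.85 = 69.4, rounded up to 70. The plan has 110.

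**Step 3. Other standard formulas, two-sided 0.05, 80% power.**

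| Formula | 10% v 30%, raw | after /0.85 | 5% v 10%, raw | after /0.85 |
|---|---|---|---|---|
| Arcsine | 59.0 | 70 | 423.7 | 499 |
| Pooled variance | 61.6 | 73 | 434.4 | 511-512 |
| Continuity-corrected | 71.2 | 84-85 | 473.6 | 558 |

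The ranges depend on whether the raw figure is rounded before the division. A one-sided alpha gives smaller numbers (at most 69 after withdrawal). No variant tried at the stated inputs reaches 110.

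**Step 4. The later steps do follow from 110.** 110 / 0.16 = 687.5. The design effect is 1 + 24 × 0.05 = 2.2. 687 × 2.2 = 1511.4, about 1512 per group, and 2 × 1512 = 3024. So the error enters at the 110 and passes through unchanged.

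**Step 5. Which comparison is larger when one formula serves both?** Dividing the preparation-stage number by 0.16:
- Arcsine: 70 / 0.16 = 438, against 499.
- Pooled: 453-456, against 511-512.
- Continuity-corrected: 84 / 0.16 = 525 to 85 / 0.16 = 531, against 558.

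The overall comparison is the larger each time. On the plan's own 499, the size is 499 × 2.2 = 1098 per group, 2196 in total. 3024 / 2196 = 1.38, so the planned trial is 38% larger.

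**Step 6. Power that the planned size gives**, with 15% withdrawal and the plan's design effect of 2.2.
- Overall, 5% v 10%: effective n = 1512 × 0.85 / 2.2 = 584 per group. Power is 90.2% (pooled) or 90.8% (arcsine).
- Preparation stage, 10% v 30%: effective n = 1512 × 0.16 × 0.85 / 2.2 = 93.5 per group, which is also 110 × 0.85. Power is 93.4% (pooled) or 94.1% (arcsine).

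**The case against.** The strongest reply is that the document shows only that 110 is not reproducible, not that it was miscalculated. The section is introduced as resting on several assumptions, and it gives no formula. Inputs that it does not state come close: 90% power with continuity correction and division by 0.85 gives about 108-109; two-sided alpha 0.01 with the pooled formula gives about 109; 90% power with two-sided alpha 0.025 and the arcsine formula gives 110. This part stands, so the point is put as an overestimate or an unstated input. It does not rescue the text: the natural reading is that the inputs at the head of the list govern both comparisons, and those inputs do reproduce 499.

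A second reply is that the subgroup can still set the size if a continuity-corrected 85 is set against the uncorrected 499 (85 / 0.16 = 532 > 499). That mixes two methods, and even then the total is 2 × 1171 = 2342.

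Third, the error is in the safe direction, and the Statistical analysis section does not depend on 110. That stands in full. A reader might infer from a wrong sample-size figure that the trial falls short of 80% power; Step 6 shows the reverse.

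A reader might also infer a still higher preparation-stage power by using a smaller design effect for the roughly four such smokers per unit (25 × 0.16). The plan applies 2.2 throughout and states no separate value, so the documents support only the 93-94%.

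Finally, 61 units per group makes 122, not 121. This is ordinary rounding (3024 / 25 = 120.96; 1512 / 25 = 60.48). The documents do not report the actual split, so none should be inferred.

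**Conclusion.** The concern holds as an error of justification. At the stated inputs the preparation-stage requirement is about 70 to 73 per group (84-85 with continuity correction), not 110. The step that makes 687 rather than 499 the basis of the total therefore does not follow, and the stated inputs support about 2196 participants rather than 3024. After 15% withdrawal, 110 corresponds to about 93-94% power, not 80%.

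The conclusion rests on two-sided testing (one-sided testing widens the gap) and on the listed power, alpha and withdrawal applying to both comparisons. It does not rest on one formula, since every standard one tried gives 85 or fewer. The power figures for 3024 also take the plan's ICC of 0.05 and cluster size of 25 as given.

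**What to change.** Restate one paragraph of the Sample size calculation section.

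1. Correct 110 to about 70-73 (84-85 if a continuity correction was used), or state the power, alpha and formula that produced 110.
2. Keep 3024 as the size and keep the record that it was derived from 687. Add that this exceeds what the stated inputs require, about 2196.
3. Report the power that 3024 gives under the design effect of 2.2 and 15% withdrawal: about 90-91% for 5% v 10% overall and about 93-94% for 10% v 30% in the preparation stage.
4. As a minor note, reconcile 61 units per group with the total of 121.

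The cost is wording only; recruitment and analysis do not change.

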### Statistical analysis

Analyses were based on the intention-to-treat principle.

Initially, an analysis of baseline comparability of the groups will be performed with respect to the variables studied. The next phase will be the estimation of raw effect on the outcome variables.

We will use multilevel analyses, with cluster as the random intercept, because of the cluster randomization. Baseline values of the dependent variable will be included as covariates.

We will describe the evolution in health-related quality-of-life (8 scales, and 2 composite measures) in participants over different time periods since quitting smoking. The SPSS statistical package (version 15) and STATA (version 10) are used throughout.

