### Study population

All the basic care units of health professionals belonging to the Spanish Preventive Services and Health Promotion Research Network (redIAPP) that expressed their intention to participate were included (n = 121). These health professionals worked in 82 primary care centres in 11 different regions of Spain.

Between the years 2003 and 2004, individuals aged between 14 and 75 years old who attended the primay care center for any reason, who answered positively to the question "Do you smoke?" and who provided informed consent to participation in the present study, were recruited. People suffering from terminal illnesses, severe psychiatric disorders, addiction to other psychoactive substances, or those unwilling to participate in the study were excluded. The recruitement continued for 12 months.

Unit of Randomization: Basic care unit. The system of randomization was centralized and computer generated.

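### The one covariate rule the article states cannot operate for abstinence, because every participant smokes at baseline; the abstinence model is left valid but without a baseline covariate

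*Protocol article*

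**What the plan says.** The Statistical analysis section of the protocol article sets out three steps after the intention-to-treat statement: a check of baseline comparability, then "The next phase will be the estimation of raw effect on the outcome variables", then the models. On the models it says "We will use multilevel analyses, with cluster as the random intercept, because of the cluster randomization" and "Baseline values of the dependent variable will be included as covariates". It names no other covariate.

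The outcome that these models mainly serve is binary: "Self reported abstinence confirmed by a breath carbon monoxide concentration of 10 parts per millions or less", as point prevalence and as continuous abstinence for a year (Outcome measures). The Objectives section measures effectiveness by continuous abstinence and names one adjustment, for the cluster randomisation.

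The Study population section restricts entry to people "who answered positively to the question" of whether they smoke. The Data collection section lists what is recorded at baseline. This includes stage of change, self-efficacy, cigarettes per day, the Fagerström test, and "motivation level measured by the Richmond test". The Sample size calculation treats stage as prognostic. It plans for 10% v 5% overall and also for "A difference of 20% between the success rate of the intervention (30%) and control group (10%) for people in the preparation stage".

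**The concern.** A baseline-value covariate is useful when the outcome varies between participants at entry. Abstinence does not vary here, because the entry criterion fixes it at zero. The only stated rule therefore adds nothing to the model for the outcome named in the objective, although the article collects several baseline variables that could do the work.

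Two things are at stake, both limited. Some precision is left unused, and the estimate has no model-based protection against chance imbalance between arms in measured predictors. There is also a practical risk. The comparability check has no stated consequence for the model, so if covariates are added for abstinence later, the documents shown do not rule out choosing them after imbalances have been seen.

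**Working it through.** **1. Does the rule add a term?** With columns for the intercept, arm and baseline abstinence (0 for all 3024 planned participants), the design matrix has rank 2 of 3. The covariate cannot be estimated and drops out. What remains is arm plus the care-unit random intercept.

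**2. The plan's own figures.** Inputs from Sample size calculation: 10% v 5%, power 80%, alpha 0.05, withdrawal 15%, 16% in preparation, design effect 2.2, 1512 per group.
- The two-sided arcsine formula gives 423.7 per group; 423.7/0.85 = 498.5, which rounds up to the stated 499.
- 110/0.16 = 687.5; 687 × 2.2 = 1511.4 per group; × 2 = 3022.8, against the stated 3024.
- The 110 itself does not reproduce by the same formula (59.0/0.85 = 69.4). That is a separate matter. Below I use only the planning rates and the stated 1512.

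**3. Rates outside the preparation stage.** This assumes that the overall and preparation-stage scenarios hold jointly, which the article does not say.
- Intervention: (0.10 − 0.16 × 0.30)/0.84 = 0.0619
- Control: (0.05 − 0.16 × 0.10)/0.84 = 0.0405
- Odds ratio for preparation v the rest, intervention: (0.30/0.70)/(0.0619/0.9381) = 6.5
- Odds ratio for preparation v the rest, control: (0.10/0.90)/(0.0405/0.9595) = 2.6

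**4. Variance removed by adjusting for preparation stage** (stage mix held at 16%, which slightly favours adjustment).

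| Arm | Total p(1 − p) | Within stage |
|---|---|---|
| Intervention | 0.0900 | 0.16 × 0.21 + 0.84 × 0.0581 = 0.0824 |
| Control | 0.0475 | 0.16 × 0.09 + 0.84 × 0.0388 = 0.0470 |
| Sum | 0.1375 | 0.1294 |

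Reduction in the variance of the risk difference: 1 − 0.1294/0.1375 = 5.9%.

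**5. Power for 10% v 5%**, from Φ(0.05/SE − 1.96) with SE = √(variance sum/effective n) and the design effect kept at 2.2 throughout.
- Full numbers, effective n = 1512/2.2 = 687.3: 94.2% unadjusted, 95.4% adjusted.
- After 15% loss, effective n = 584.2: 90.3% unadjusted, 91.9% adjusted.

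**6. Effect of chance imbalance.** Arm-averaged rates are 20% in preparation and 5.1% otherwise, a gap of 14.9 points. The standard error of the difference between arms in preparation share is √(2 × 0.16 × 0.84 × DE/1512). The article gives no intracluster correlation for stage, so a range is shown at 25 patients per unit.

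| Assumed ICC for stage | DE | SE of imbalance | Shift in risk difference at 1 SE |
|---|---|---|---|
| 0 | 1.0 | 1.3 points | 0.2 points |
| 0.05 | 2.2 | 2.0 points | 0.3 points |
| 0.10 | 3.4 | 2.5 points | 0.4 points |

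A 5-point imbalance would shift the unadjusted difference by 5 × 0.149 = 0.7 points against a target of 5. At ICC 0.05 that is about a 2.5-SE event.

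**The case against.** The best defence is that a covariate list belongs in the full protocol or analysis plan, which are not shown, and that the article nowhere says other covariates are excluded. That is right, and the absence of a list is not the point made here. The point is that the rule the article does state cannot operate for its main outcome, and the article does not limit the rule to outcomes where it can. The rule does have a natural target in stage of change. SF-36 also has a baseline value, but its evolution is only to be described.

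Second, the model that remains is sound. Arm plus a random intercept respects the randomisation and matches the adjustment named in the objective. This stands in full. A reader might infer that the main analysis is biased or ignores clustering; the documents support neither.

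Third, a reader might take the odds ratios of 2.6 and 6.5 as the size of the damage. They describe prognosis. The cost to the trial is the 6% of variance and the small shifts in the working, and even those depend on combining scenarios that the article introduces as different assumptions.

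Fourth, a reader might infer that the authors meant the rule to shield the abstinence estimate from imbalance or selective enrolment. No section states such a purpose, and covariates would in any case not remove selection on unmeasured factors.

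Fifth, baseline stage may not be measured alike in both arms. The intervention has stage asked at the visit by staff who, in that arm, had special training, and the article does not say whether stage sits in the clinical part of the questionnaire or in the part given by blinded telephone interviewers. This is a fair caution about which measurement to use.

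One counter-argument fails. The Description of the intervention mentions action and maintenance stages, which might suggest that some participants were already abstinent at entry. Entry still required a yes to smoking, and the same section says that later interventions follow each person's evolution.

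**Conclusion.** The concern holds in a limited form. The stated rule adds no estimable term for abstinence, and this follows from the entry criterion alone, without further assumptions. As written, the abstinence model has no baseline covariate. It remains valid under randomisation and accounts for clustering.

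What is forgone is small: about 6% of the variance of the risk difference, 1 to 2 points of power in a design already above 90% for 10% v 5% on the stated numbers, and protection against shifts of roughly 0.2 to 0.4 points for a one-standard-error imbalance in preparation stage. These sizes assume that the two planning scenarios hold together, that the design effect of 2.2 applies before and after adjustment, and that the intracluster correlation for stage is between 0 and 0.10. They cover preparation stage only; the article gives no figures for the gain from other predictors. Severity is minor to moderate: the rule should be corrected, but the trial's conclusion does not hang on it.

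**What to change.** Restrict the baseline-value rule to outcomes that vary at baseline, such as stage of change. For the abstinence outcomes, name a short fixed list of covariates already collected, to enter the random-intercept model at patient level: at minimum baseline stage of change and Fagerström score, with age and sex. Say which baseline measurement of stage is used. The Richmond score overlaps with stage and need not be added.

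Fix the list before outcomes are compared by arm. Recruitment ran in 2003–2004 with two years of follow-up, so the amendment should be dated and should say whether any comparison by arm had been seen. If one had, label the adjusted analysis as post hoc.

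Report the raw estimate alongside. The adjusted odds ratio is conditional on the covariates and is not directly comparable with the raw one, so add a standardised risk difference.

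The cost is a few sentences of analysis text and one extra reported estimate, with no new data. Adjustment should not be presented as a remedy for selective enrolment on unmeasured factors.
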